### Moderators

*Student, parent and trainer characteristics*, including age, gender, ethnicity and education level will be collected at baseline. Parents will also report family characteristics and information about work and education level (as indicator of SES), and trainers will report information about their level of experience, perceived competence and educational background. Finally, students and parents will report their expectations for the skills-training program (at baseline) and will evaluate the program (post-intervention measurement).

*Positive parenting behavior* will be measured with the Dutch Abbreviated Scale of Parenting Behavior (VSOG) [85], completed by parents. This instrument is a 25-item self-report for parents with five subscales. In this study only the subscale positive parenting behavior will be used, which consists of 8 items (e.g., “I make time for my child, when he/she wants to tell me something”). The subscale has a Cronbach’s alpha of .83 for mothers and .87 for fathers [85].

*Social support* will be measured with the Social Support List – Interactions (SSL-I) [86], adapted for use in adolescents. It measures the extent of received social support by social interactions in an individual’s social network. The instrument consists of 12 items (e.g., Does it ever happen to you that people: “are interested in you” or “ask you for help or advice”?) and three subscales (i.e., everyday social support, social support in problem situations and esteem support) and has acceptable internal consistency for all subscales (.70 or above) [86, 87].

*Perfectionism* will be measured with the Child and Adolescent Perfectionism Scale (CAPS-14) [88], translated into Dutch. This instrument is a 14-item self-report measuring perfectionism and consists of three subscales: self-oriented perfectionism-striving (3 items, e.g., “I try to be the best at everything I do”), socially prescribed perfectionism (7 items, e.g., “Other people always expect me to be perfect”) and self-oriented perfectionism-critical (4 items, e.g., “I get mad at myself when I make a mistake”). The internal consistency of the subscales is between .72 and .86 [88].

S*tressful life events* will be measured with the Negative Life Events Inventory [89, 90], translated into Dutch. This instrument is a 20-item checklist of negative life events (e.g., “Somebody in my family had a serious illness”). Students are asked to indicate whether an event had occurred during the previous year and includes events that occurred to family members and directly to themselves. The internal consistency is between .67 and .71 [89, 90]. Students will complete this instrument after completion of the skills-training program (post-intervention measurement).

*Perceived parental pressure* will be measured with the subscale parental pressure of the Multidimensional Inventory of Perfectionism in Sport (MIPS) [91], translated into Dutch. The perceived parental pressure subscale consists of 8 items (e.g., “My parents set extremely high standards for me”). The internal consistency is good (above .92) [91, 92]. Parental pressure has a high temporal stability [93] and students will therefore complete this instrument at post-measurement.

*Treatment alliance* will be measured with the Therapy Alliance Scale for Children (TASC) [94], translated into Dutch and altered for use in group skills-training programs. This is a 12-item instrument measuring the bond-aspect of alliance (6 items, e.g., “I like my trainer”) and the tasks of the program (6 items, e.g., “I work with my trainer on solving my problems”). This instrument has good internal consistency (above .70) [95, 96] and is completed by students after completion of the skills-training program (post-intervention measurement).

*Program integrity* will be measured with a questionnaire specifically developed for this study. After each session, trainers will be asked to evaluate the session by registering if they carried out the session as intended (e.g., is the content of the session sufficiently treated, are other components discussed, and what was their overall impression of the session).

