For instance, high levels of social support have been positively associated with well-being and mental health in children and adolescents [38, 39]. Moreover, high levels of social support have been associated with a more beneficial psychological treatment outcome in clinical samples [40, 41]. High occurrence of stressful life events has been associated with stress-related psychopathology and negative mental health outcomes, such as anxiety, depression and risk behavior [42–44] and predicts adverse treatment outcome [45]. On the one hand, high social support and low occurrence of stressful life events are associated with more beneficial outcomes. On the other hand, several studies showed larger program effects for adolescents with high initial problem severity [46, 47]. Following this line of reasoning, it may also be possible that students with low social support or with high occurrence of stressful life events profit most from the skills-training programs, because the sessions provide them with tools that are not provided by their social network.

Perceived stress positively correlates with perfectionism [48] and perceived parental pressure [49], which have been associated with mental health problems such as anxiety and depression [50–52]. Previous studies showed that perfectionism and maternal rejection (i.e., less emotional warmth), the latter associated with parental pressure [52], are related to less beneficial treatment outcomes in children and adolescents with anxiety or depression [53–56]. It is therefore expected that students with higher levels of perfectionism or students who perceive more parental pressure may benefit less from the skills-training programs.

Parent characteristics that may affect the effectiveness of the skills-training program include demographic characteristics (i.e., educational level) and positive parenting behavior. Positive parenting behavior increases adolescents’ social competence reflecting positive functioning at school including peer competence and attachment to school [57], and improves the relationship between parent and adolescent [58]. Because of this warm relationship, parents may be more involved in the life of their child and students may feel more confident to talk about the program at home. It is therefore expected that the skills-training programs are more effective for students with parents that show more positive parenting behavior.

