### Data collection

Questionnaires assessing program targets (i.e., skills to deal with performance anxiety or social skills), specific goals of the skills-training programs (i.e., performance or social anxiety) and mental health (i.e., stress, internalizing and externalizing behavior, well-being and self-esteem) will be completed by students and parents prior to the start (T1) and after completion of the interventions in the experimental group (T2). Trainers complete questionnaires about program content (to assess program integrity) after each training session. Additionally, in a subsample of students (approximately *N* = 40 students per skills-training program), physiological parameters will be measured during a resting period to assess the basal stress levels of students (i.e., heart rate, heart rate variability and skin conductance measurements with wearables).

Student and parent characteristics (i.e., demographics including gender, age, ethnicity and education level, and expectations about the program) are assessed prior to the interventions, as well as trainer characteristics (i.e., demographics including gender, age, ethnicity, education level, and level of experience and perceived competence). Lastly, after completion of the intervention, students, parents and trainers will evaluate the skills-training program.

The design of this study has been approved by the Ethical Committee Psychology of Leiden University (CEP18–1105/419) and is registered in the Dutch Trial Register (number NL7438). To maintain participant confidentiality, all records that contain names or other personal identifiers will be stored separately from the collected data identified by code numbers.

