### Interventions

Students in the experimental condition of each skills-training program will participate in seven 45-min small-group sessions during consecutive weeks. Weekly sessions will take place at the school of the students and the sessions will be delivered by an experienced trainer or trained teacher in small groups. The performance anxiety skills-training program consists of cognitive coping strategies (e.g., negative thought restructuring and managing emotions), relaxation techniques and dealing with pressure. The social skills training program consists of social skill building (e.g., identifying personal qualities, giving own opinions, setting boundaries, and standing up for yourself) and cognitive coping strategies (e.g., managing emotions).

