### Waitlist-control group

The waitlist group will not receive any training during the implementation of the intervention in the experimental group and will only complete the pre-and post-intervention measurements. The waitlist group will receive the intervention immediately after the post-intervention measurements, approximately 8 weeks later than the experimental group.

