### Statistical analyses

To examine the effectiveness of the skills-training programs, the effects of all outcome measures will be investigated by conducting analyses of covariance (ANCOVAs). The dependent variables are the outcome measures at post-test (program targets, direct program outcomes and mental health outcomes), the independent variables are the conditions and the covariates are the pre-test (baseline) measurements of the outcome measures. The effect of potential categorical and continuous moderators on the effectiveness of the skills-training programs on the specific goals of the programs and mental health of students will be examined by adding the moderators to the ANCOVAs. Data will be imported from an online server software (i.e., Qualtrics) and will be securely stored at the server of Utrecht University where data back-ups will be performed regularly.

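### Perceived parental pressure, and less seriously stressful life events, are measured only after training and then used as moderators, so moderation results can be distorted

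*Protocol article*

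**What the plan says.** Table 1 of the protocol article lists the Negative Life Events Inventory and the MIPS parental pressure subscale under student characteristics, as moderators, with T2 as the only time of measurement. The Moderators section confirms this. For life events: "Students will complete this instrument after completion of the skills-training program (post-intervention measurement"). The recall period is one year: "Students are asked to indicate whether an event had occurred during the previous year". For parental pressure: "Parental pressure has a high temporal stability [93] and students will therefore complete this instrument at post-measurement". No reason is given for the timing of life events.

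The Data collection section places T2 after the experimental group has completed its program. The waitlist arm is still untrained at that point: "The waitlist group will receive the intervention immediately after the post-intervention measurements, approximately 8 weeks later than the experimental group".

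The Statistical analyses section says that the effect of moderators "will be examined by adding the moderators to the ANCOVAs". It does not treat those measured after training differently from those measured before. The Background states a directional hypothesis for pressure: "students who perceive more parental pressure may benefit less from the skills-training programs". Social support, perfectionism and positive parenting are measured at T1.

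**The concern.** A moderator is meant to describe students as they were before training. Measured at T2, the score is taken after training in one arm and before it in the other. Comparing arms at the same T2 score then compares like with like only if training leaves the score alone.

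The article itself supplies a route by which it might not. The performance anxiety program includes negative thought restructuring, and also "relaxation techniques and dealing with pressure". The moderator is the student's perception of parental demands. If students who gain most also come to report less pressure, those still reporting high pressure will be the ones who gained least. That is the pattern the Background predicts, and it would appear with no true moderation.

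Moderation is the second declared aim, and the Discussion presents it as an advance on earlier trials. A baseline score that was never collected cannot be recovered by later analysis, so the timing matters more than the modelling detail.

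**Working it through.** **1. The plan's own figure.** The Study sample section gives N = 130 per program, power .80, alpha .05 and a medium effect of .25. Read as Cohen's f (d = 2 x 0.25 = 0.5), an ANCOVA F test with 1 numerator df, one covariate and noncentrality N x f² needs N = 128 (power 0.801). N = 130 gives 0.808. The figure reproduces, and this point does not dispute it. It supplies N and the average benefit of 0.5 SD used below.

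**2. Model (all other values are assumptions).** There are 65 students per arm, T = 0 or 1, and the outcome is an anxiety score on which lower is better:

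- Outcome: Y = 0.6 Y0 - T(0.5 + 0.5u) + b M0 + g T M0 + 0.8e, where u is individual response to training, M0 the baseline moderator, b its slope on the outcome and g the true moderation.
- T2 moderator: M2 = r M0 + √(1 - r²) e' - s T - k T u, where r is stability, s the average shift caused by training and k the part of the shift that follows individual benefit.
- Analysis: ANCOVA on T, Y0, M and T x M.

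The slope of Y on M2 is b r in the waitlist arm and [(b + g) r + 0.5k] / (1 + k²) in the trained arm. The interaction estimated from M2 is therefore

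[(b + g) r + 0.5k] / (1 + k²) - b r.

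The average shift s does not appear in it. A positive value means that higher reported pressure goes with less benefit, which is the hypothesised direction.

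**3. Results with no true moderation (g = 0, r = 1).**

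| Assumed effect of training on the T2 score | Formula | Simulated interaction | Rejection at 5% |
|---|---|---|---|
| None | 0 | about 0 | 5% |
| Uniform shift s = 0.3, k = 0 | 0 | 0.00 | 5% |
| s = k = 0.3, b = 0.4 | 0.55/1.09 - 0.40 = 0.105 | 0.11 | 11% |
| s = k = 0.3, b = 0 | 0.15/1.09 = 0.138 | 0.14 | 15% |
| s = k = 0.5, b = 0 | 0.25/1.25 = 0.20 | 0.20 | 27% |

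The baseline moderator M0 gives about 0 and 5% throughout.

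**4. Results with true moderation (r = 1, b = 0).**

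- g = -0.30: the baseline moderator recovers -0.30. The T2 moderator gives (-0.30 + 0.15)/1.09 = -0.14 at k = 0.3 and (-0.30 + 0.25)/1.25 = -0.04 at k = 0.5.
- g = +0.30 (the hypothesised direction): the T2 moderator gives (0.30 + 0.15)/1.09 = 0.41 at k = 0.3, an overstatement.
- Training does not touch the score and stability is r = 0.8: -0.30 only attenuates to 0.8 x -0.30 = -0.24, and the 5% error rate is kept.

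These runs tie the individual shift perfectly to individual benefit. A looser link gives less: at correlation 0.5 with k = 0.3 and b = 0, the spurious interaction is 0.075/1.09 = 0.07.

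**5. Life events window.** About 8 of the 52 weeks recalled at T2 follow the start of training: 8/52 = 15%. The other 85% precede it.

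**6. Questionnaire load (student items stated in the article, assuming every student completes every scale).** Outcomes: 18 + 47 + 5 + 20 + 9 + 19 + 30 + 5 + 10 = 163. T1 adds social support (12) and perfectionism (14), total 189. T2 adds life events (20), parental pressure (8) and alliance (12), total 203. Demographics, expectations, program evaluation and the mood scales for the physiological subsample are not counted.

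**The case against.** The case for leaving the timing alone has real content.

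- **A uniform shift is harmless to a linear interaction.** This stands. Bias needs the shift to vary with individual benefit, which is plausible when the same skills drive both but is not shown. A uniform shift would still change who falls on which side of a fixed cut-off, if one were used.
- **The mechanism is inferred.** The program description speaks of pressure in general, not of parental pressure, and the sample item describes what parents do rather than how the student copes. This content is listed only for the performance anxiety program. The route is therefore weaker for the social skills program. It is not excluded for the other, because the scale measures a perception.
- **Life events are mostly external.** A short school program will not cause a serious illness in the family, and about 85% of the window precedes training in both arms. What remains is altered reporting, or events during the training weeks. The risk is much smaller than for pressure.
- **The baseline session is already long.** This is fair: the Discussion relies on brief questionnaires for participation and retention. Moving only the pressure subscale adds 8 items.

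A reader might infer that the estimated training effect is itself diluted, because a T2 score shifted by training would absorb part of it. The documents do not support that. The effectiveness ANCOVAs adjust only for baseline values of the outcomes, and moderators enter only for the separate moderator question.

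**Conclusion.** The concern holds for the moderator analysis and should be fixed, chiefly for perceived parental pressure in the performance anxiety trial and as a lesser matter for life events. The stated justification does not support the choice: stability does not show that a rating is unaffected by training, and a stable rating could be taken at T1 without this risk.

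The size is unknown. If training shifts the rating by 0.3 to 0.5 SD in step with benefit, false-positive moderation at N = 130 rises from 5% to roughly 11-27%, and a true interaction can shrink or be overstated. These rates rest on assumed inputs and on a tight link between shift and benefit, so they show what is possible and not what to expect. If training leaves the rating alone, the loss is modest attenuation. The main comparison of each program with waitlist is not in question. Treatment alliance and program integrity are also recorded at T2, but they describe the training process itself and fall outside this point.

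**What to change.** - Move the 8-item MIPS parental pressure subscale to T1. Change its row in Table 1 and the sentence in the Moderators section that justifies the T2 timing.
- Preferably move the 20-item Negative Life Events Inventory to T1 as well. If it stays at T2, ask only about events before the start of training. That removes the overlap with the training weeks but not the possibility of altered recall.
- For students already past T1, label the T2-based moderator results exploratory and report the arm difference in each moderator. State that finding no difference does not prove the moderator was unaffected.

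Cost: sample size and total length are unchanged. Moving the pressure subscale takes the student set at T1 from about 189 to 197 items and at T2 from about 203 to 195. Moving both gives about 217 at T1 and 175 at T2. The price is a longer baseline session: about 4% longer for the subscale alone (8/189) and 15% for both (28/189).

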### Statistical analyses

To examine the effectiveness of the skills-training programs, the effects of all outcome measures will be investigated by conducting analyses of covariance (ANCOVAs). The dependent variables are the outcome measures at post-test (program targets, direct program outcomes and mental health outcomes), the independent variables are the conditions and the covariates are the pre-test (baseline) measurements of the outcome measures. The effect of potential categorical and continuous moderators on the effectiveness of the skills-training programs on the specific goals of the programs and mental health of students will be examined by adding the moderators to the ANCOVAs. Data will be imported from an online server software (i.e., Qualtrics) and will be securely stored at the server of Utrecht University where data back-ups will be performed regularly.

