In sum, the current protocol describes a study that will be conducted to examine the effectiveness of two types of targeted school-based skills-training programs addressing skills to deal with performance anxiety (program 1) and social skills (program 2). In order to overcome some of the limitations of previous studies, small-group skills-training programs are evaluated in a mixed-ethnicity community sample of students with different educational levels, where students self-select to one of the skill-training programs. For each program, a RCT is performed to examine if these low-threshold interventions reduce performance or social anxiety and promote students’ mental health. Both skills-training programs will be compared to a control waitlist condition. As illustrated in Fig. 1, it is expected that the performance anxiety skills-training program will improve skills to reduce performance anxiety (i.e., coping skills, including negative thought restructuring and managing emotions), resulting in a reduction in students’ performance anxiety (i.e., fear of failure and test anxiety) and in improved mental health (i.e., reduced stress and internalizing and externalizing problems, and increased well-being and self-esteem). Additionally, we expect that the performance anxiety skills-training program will directly reduce performance anxiety and improve mental health. It is expected that the social skills-training will improve students’ social skills and thereby reduce their social anxiety and improve their mental health (i.e., reduced stress and internalizing and externalizing problems, and increased well-being and self-esteem). In addition, we expect that the social skills training program will directly reduce social anxiety and improve mental health (see Fig. 1). The second aim is to investigate the moderators of the effectiveness of both skills-training programs on all outcomes. This is important because it is likely that the skills-training programs are not equally effective for all students. Student, parent and program characteristics will be examined as potential moderators. The final aim of this study is to evaluate if the school-based skills-training programs are experienced as sufficiently accessible, meaningful and helpful by the students, their parents and the trainers. Figure 1 shows a conceptual model of the research design.

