## Methods/Design

### Design

A RCT will be conducted for both school-based skills-training programs targeting: 1) skills to deal with performance anxiety and 2) social skills. For each skills-training program, students who have indicated interest in attending a training at their school, will be randomized by the first author (stratified for education level) into the experimental group in which the training starts immediately or into a waitlist control group that receives the training approximately eight weeks later (see Fig. 2), using computerized randomization in a 1:1 ratio. We will use a multi-method (questionnaires and physiological data) and a multi-informant (students, parents and trainers) design and will recruit a mixed-ethnicity sample of students from different educational levels.

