### Study sample

For each school-based skills-training program we aim to include *N* = 130 students to ensure there is enough power for the analyses (*N* = 65 for both the experimental and waitlist control group). A total of *N* = 260 students will be included. This sample size is sufficient to investigate the effectiveness of the interventions and potential moderators, with a power of .80, an alpha of .05 and a medium effect size of .25 [63].

Participants are mixed-ethnicity students in the first, second, and third year of secondary schools (7th, 8th and 9th Grade students) of at least three schools in the Netherlands that offer education at various levels (from vocational education level to preparatory university education level). The students will be between 11 and 16 years old.

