### Direct program outcomes

*Performance anxiety* will be measured by two instruments measuring different domains, i.e., fear of failure and test anxiety, completed by students and parents. For parents, adapted versions are used where “I” is replaced by “my child”. The short form of the Performance Failure Appraisal Inventory (PFAI) [69] will be used, translated into Dutch. The PFAI is a 5-item self-report instrument measuring fear of failure (e.g., “When I am failing, I am afraid that I might not have enough talent”) with good reliability (internal consistency between .72 and .82) [69, 70]. The Dutch short version of the widely used Spielberger Test Anxiety Inventory (TAI) [71, 72] will be used to assess anxiety in school testing situations. This instrument consists of 20 items (e.g., “I feel confident and relaxed while taking tests”) and has demonstrated adequate internal consistency (between .92 and .96) [73].

*Social anxiety* will be measured with the social phobia scale of the Dutch version of the Revised Child Anxiety and Depression Scale (RCADS) [74], completed by students and parents. For parents, an adapted version will be used where “I” is replaced with “my child”. This instrument consists of 9 items (e.g., “I worry what other people think of me”) and has good internal consistency (between .78 and .81) [74, 75].

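### No primary outcome is named: each programme's effectiveness rests on about 7–11 outcome tests, while the sample size is set for one test at alpha .05

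*Protocol article*

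**What the plan says.** The Statistical analyses section of the protocol article ties the effectiveness question to every outcome: "the effects of all outcome measures will be investigated by conducting analyses of covariance (ANCOVAs". The dependent variables are listed as three families, "program targets, direct program outcomes and mental health outcomes", with nothing to say which of them decides. No other section names a primary outcome.

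The Study sample section plans 130 students per programme, "students to ensure there is enough power for the analyses", and gives one set of design values: "with a power of .80, an alpha of .05 and a medium effect size of .25". That is the only alpha in the article, and it is attached to no particular outcome.

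Several outcomes have more than one scale or informant. Performance anxiety, for example, is measured as "fear of failure and test anxiety, completed by students and parents".

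On moderators, the Background states: "The second aim is to investigate the moderators of the effectiveness of both skills-training programs on all outcomes". The Statistical analyses section is narrower: it applies the moderators to the programmes' specific goals and to mental health, and leaves out program targets.

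**The concern.** If several outcomes bear on one conclusion and none is marked as decisive, the 5% error rate belongs to each test and not to the conclusion. A programme with no effect would then have several chances to produce a significant result, and the article gives no rule for a mixed picture, such as improved self-esteem with unchanged test anxiety. The sample size matters too. It supports one test at .05, so correcting later for all outcomes would use up the stated power. Which outcome decides the trial is a protocol-level choice, and it has to be made before the data are seen.

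**Working it through.** **1. The plan's own figure.** Inputs from Study sample and Design: N = 130 per programme, 65 per arm ("using computerized randomization in a 1:1 ratio"), alpha .05, power .80, "a medium effect size of .25". Sidedness is not stated; the F-test (two-sided) is assumed. Read as Cohen's f, for a two-group ANCOVA with one covariate:

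- noncentrality = N × f² = 130 × .0625 = 8.125, with 1 and 127 degrees of freedom;
- power at N = 130 is .808, and the smallest even N reaching .80 is 128.

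The plan's figure is reproduced as one test. Read as Cohen's d, .25 would need N = 504 (power .30 at 130), so f is the intended scale.

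**2. Counting tests** (Table 1 and the outcome sections). It is assumed that each programme is tested on its own target and direct outcome plus the shared mental health outcomes, with one score each for CERQ-short and SIG-A, and with internalizing and externalizing problems kept separate.

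- Performance anxiety, students: CERQ-short, PFAI, TAI, CSQ-CA, internalizing, externalizing, WHO-5, RSES = 8. Parents: PFAI, TAI, CSQ-CA = 3. Total 11.
- Social skills, students: SIG-A, RCADS social phobia and the same five mental health scores = 7. Parents: SIG-A, RCADS social phobia, CSQ-CA = 3. Total 10.

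**3. Chance of at least one p < .05 if there is no effect.** Independent tests: 1 − .95^m. Correlated tests: equicorrelated normal statistics, integrating over the shared component W,

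1 − E{[Φ((c − √r·W)/√(1 − r)) − Φ((−c − √r·W)/√(1 − r))]^m}, with c = 1.96.

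The correlations are assumptions; the article gives none.

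| m | Independent | r = .3 | r = .5 | r = .7 |
|---|---|---|---|---|
| 7 | .302 | .271 | .230 | .178 |
| 8 | .337 | .300 | .250 | .191 |
| 10 | .401 | .351 | .287 | .213 |
| 11 | .431 | .375 | .304 | .223 |

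**4. Errors in the beneficial direction only** (.025 per test; independent tests: 1 − .975^m).

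| m | Independent | r = .3 | r = .5 |
|---|---|---|---|
| 7 | .162 | .137 | .115 |
| 8 | .183 | .152 | .125 |
| 10 | .224 | .178 | .144 |
| 11 | .243 | .191 | .152 |

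**5. Most favourable reading: only the direct program outcomes decide.** Performance anxiety has two scales × two informants = 4 tests: 1 − .95⁴ = .185. Social anxiety has one scale × two informants = 2 tests: 1 − .95² = .0975. Both assume independence and are lower if the tests correlate.

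**6. Correcting for all outcomes instead.** Bonferroni over 8 tests: .05/8 = .00625, power at N = 130 is .53, and N = 210 is needed for .80. Over 11 tests: .05/11 = .0045, power .49, N = 222.

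**7. Moderators, counted separately.** The Background lists 11 student, 2 parent and 5 program moderators. The five program ones (alliance, integrity, trainer ethnicity, experience, competence) describe delivered training, which the waitlist group has not had by T2, so an ordinary condition-by-moderator interaction cannot be estimated for them. That leaves 13. Without program targets, the outcomes are 4 + 6 = 10 for performance anxiety and 2 + 6 = 8 for social skills. If each is tested at .05: 13 × 18 × .05 = 11.7 expected false moderation findings.

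**The case against.** The article condenses a fuller plan, and a multiplicity procedure may sit in an analysis plan that is not shown. That stands, and the absence of such a procedure is not the point here. The point is what the article does fix: effectiveness judged on every outcome, with a sample sized for one test.

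The outcomes are also not a flat list. They are sorted into targets, direct outcomes and mental health, the conceptual model runs from skills to anxiety to mental health, and Data collection treats performance or social anxiety as the programmes' specific goals. This is a fair indication of priority, but it is not a testing order. The Background also expects direct effects on mental health, and the direct outcomes alone still comprise four tests and two tests.

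Three stronger readings are tempting, and the document does not support them:

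- A reader might infer a chance of one in three or more of falsely declaring a programme effective. That is not a floor even for two-sided errors: student-report outcomes alone give .23–.30 at correlations of .3–.5. A false claim of effectiveness also requires an error in the beneficial direction, which roughly halves the figures.
- A reader might infer that the plan tests every outcome and moderator at .05, or accepts any significant result as proof. Neither is written; .05 appears only in the sample-size sentence.
- A reader might cross all 18 moderators with all outcomes and expect about 20 false positives. That count includes program targets, which the analysis section leaves out, and moderators with no waitlist counterpart. Moderator tests cannot produce a false main effect in any case.

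The test counts depend on choices. Two CERQ composites would make 12 tests for performance anxiety (.46 if independent). Three physiological measures and one VAMS score would make 15 and 14 (.54 and .51), but the physiological measures are taken in only about 40 students per programme.

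**Conclusion.** The concern holds in this form: the article does not say which result decides whether a programme works, and followed as written it does not hold a 5% error rate for that conclusion. The excess is moderate to large under every count and correlation examined: 18–43% for any false-positive result across 7–11 tests, with correlations from 0 to .7. For beneficial-direction errors it is 11.5–24% with correlations from 0 to .5. These figures assume .05 per test, one score per instrument and equal correlations, so they are illustrations and not properties stated in the plan. The gap does not depend on them, because even the narrowest reading leaves more than one deciding test per programme. The moderator figure of about 12 concerns false moderation findings only and rests on an assumed count.

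**What to change.** Before outcome data are seen, name one student-reported T2 primary outcome per programme, taken from the existing direct program outcomes and tested at two-sided .05:

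- **Social skills programme:** RCADS social phobia, the only student scale in that family.
- **Performance anxiety programme:** one prespecified choice, such as TAI, PFAI or a prespecified composite of the two. The article defines performance anxiety by both fear of failure and test anxiety, so the choice is the sponsor's.

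Because the two programmes are separate trials, each can keep its own .05.

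Label the remaining outcomes secondary, with a stated multiplicity rule; Holm within programme is one suitable option. Describe parent-report, physiological and moderator results as supportive or exploratory. Reconcile the Background and Statistical analyses sections on which outcomes the moderators apply to, and report those tests as a separate family.

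This needs about one paragraph, with the registry entry brought into line where it differs, and no extra students. The downside is stricter thresholds for secondary outcomes and a commitment to one measure per programme.
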